### Secondary outcome measures

All participants are asked to complete several quality of life questionnaires and hearing tests at inclusion and 6 months after their choice of the treatment (abstention, CROS hearing aids, BAHA, cochlear implantation). Pre/post treatment analyses will be carried out in each of these groups. Comparisons will be made in the group of subjects who chose a CI, randomised between immediate CI and initial observation.

### Quality of life

As described above, a generic evaluation of quality of life is performed using the EuroQol-5D-3 L scale. Hearing-specific quality of life questionnaires will also be administered.

The Nijmegen Cochlear implant questionnaire (NCIQ) contains 60 questions exploring 6 areas concerned with the quality of auditory perception (basic perception, complex perception, speech production, self-esteem, social activities and interactions) [43]. Indeed, the perception of basic environmental sounds such as bells or footsteps is assessed as well as oral communication with new contacts. Each item is formulated as a statement with a 5 point response scale to indicate the degree to which this statement is judged true (from “never”:1 to “always”:5). An extra point can be chosen if none of the points fits.

An evaluation of the discomfort related to the possible tinnitus associated with the deafness will rely on a visual analogue scale (VAS) ranging from 0 to 10. This scale is presented as a 17 cm plastic ruler with a vertical arrow on one side and a graduated scale on the other side (0 to 10 cm). The subject first indicates the level of annoyance generated by the tinnitus on the vertical arrow using a cursor and the corresponding numeric value is reported by the evaluator. Then, the intensity of tinnitus is assessed using another ruler with the same dimensions.

### Speech understanding in noise

Speech recognition in competing noise is measured using the French Matrix test [44] in sound field (IAC 120A-1 sound booth). The French Matrix test is a closed-set sentence test that uses 50 well-known words in French. Each sentence has the same syntactic structure: name - verb - number - object – colour, for example: “Felix draws six blue bikes”. The number of combinations of five words is large enough to eliminate memory-based responses. Speech and noise signals are generated from an IBM PC running the OMA software (www.hoertech.de) and presented via loudspeakers and amplifier (Studio Lab, SLB sat 200). Speech signal is presented at a fixed level of 65 dB SPL and the level of competing noise is adjusted using the adaptive procedure described by Jansen et al. to obtain the signal-to-noise ratio in dB for 50% correct word recognition (SNR50).

SNR50 is obtained in three different spatial configurations: one with speech and noise presented from a single loudspeaker in front of the subject at 0° and two conditions with speech and noise presented from separate loudspeakers at 60° to the left and right of the subject. The choice of a spatial configuration (− 60°, 0° and + 60°) was selected based on previous results [45] showing that when such positions are used, the head-shadow effect is reduced while the binaural unmasking is maximised compared to a ± 90° configuration. The “dichotic” condition is defined as speech presented to the poorer hearing ear and the noise to the contralateral, normal hearing ear; the diotic condition as both the signal and the noise presented from the loudspeaker located in front of the subject; and the reverse dichotic condition with speech presented to the normal hearing ear and noise to the poorer ear. Subjects will be asked to repeat any word which is heard.

### Auditory horizontal localisation

Horizontal localisation ability is assessed using an array of 7 horizontal loudspeakers and an amplifier (Studio Lab, SLB sat 200) located at intervals of 30 degrees from – 90 degrees to 90 degrees in a frontal semicircle diameter of 1.2 m at the subject’s head level. The stimulus comprises two 150 msec white gaussian noises from 20 Hz to 20 kHz with a 0.05 msec ramp. A silence of 150 msec is inserted between the two noises for total stimulus duration of 450 msec. This stimulus is similar to the one used by Slattery and Middlebrooks [46] and is presented 63 times (9 presentations per loudspeaker) with a period of 2 s silence between each presentation to allow the subjects to indicate orally the loudspeaker location. Subjects are asked to not move their head during the experiment: this was controlled by the examiner. Localisation ability measurements are the rate of correct localisation and the root mean square error.

### Statistical methods, data reporting and analysis

Once the validity of the database is double-checked, descriptive analyses will be carried out for each treatment option (observation, CROS hearing aids, bone conduction device, cochlear implant). Quantitative variables will be described as means, standard deviations, and percentile distribution. The number and proportion of subjects will be used to describe categorical data.

Regarding the randomised controlled trial phase comparing CI versus observation, the analysis will be conducted on all subjects who were randomised on an intention-to-treat basis. For each outcome (quality of life, hearing performances indicators), the value measured at 6 months will be compared between the two groups using bivariate analyses (Student’s T test or Wilcoxon rank sum tests) and linear regressions adjusted for the baseline value.

For each intervention, we will assess the associations between changes in hearing performances and changes in quality of life. Data will be presented according to the Consolidated Standards of Reporting Trials (CONSORT) Statement [47, 48].

In order to test the robustness of the ICUR, deterministic and probabilistic sensitivity analyses will be conducted.

As part of the sensitivity analysis, we will determine the robustness of the results by testing the impact on the outcome of the variation of different cost and utility parameters [40]. Probabilistic sensitivity analysis, performed using the non-parametric bootstrap method, identified the uncertainty around the ICUR by estimating its confidence interval [49]. Moreover, a Cost-Utility Acceptability Curve (CUAC) will be built to summarise the impact of uncertainty on the ICUR in relation to possible values of the cost-effectiveness threshold [50].

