## Methods

### Study design and setting

This prospective multicentre national study combines two major steps:

- a prospective, descriptive observational cohort study, with a 6-month follow-up for SSD/AHL adult subjects treated by CROS, SSD/AHL subjects treated by an implanted bone conduction device (Baha or Ponto), and adult patients who decline all the options.

- and an open-label randomised controlled clinical trial for adults with SSD or AHL after failure of both CROS and BC systems, in two parallel groups: Observation for 6 months versus Cochlear implantation.

Participants are recruited in 7 tertiary referral centres in France. Once the inclusion/criteria are checked and the consent from the subject is obtained by one of the investigators, a reference evaluation is made for quality of life, binaural hearing performances (i.e. speech recognition in noise and horizontal localisation) and tinnitus severity. Then, CROS hearing aids and a BC device on a headband are successively tried by the subjects for three weeks each. The evaluation of quality of life, binaural hearing abilities, and tinnitus severity is repeated after the first trial (CROS) and the second trial (BC). At this point, the subject may choose the treatment he/she is willing to continue. If one of the trials (CROS or BC) is considered to be successful and the subject is willing to continue with the corresponding device, it is then provided and a new evaluation is performed 6 months later. If none of the trials is considered to be successful and the subject does not want any other treatment, then only a new evaluation is performed 6 months later. If none of the trials is considered to be successful and the subject wants treatment by cochlear implantation, the second major step of the study begins with the randomisation procedure.

Subjects who chose a cochlear implant are thus randomised between two arms: in the first one (“CI” arm), a cochlear implantation is performed within a month and a new evaluation on quality of life, binaural hearing performances, and tinnitus severity is planned 6 months after CI activation. Subjects of the second arm (“observation” arm) simply undergo the new evaluation 6 months after randomisation, without any intercurrent treatment for SSD/AHL. For obvious ethical reasons, subjects of the second arm benefit from a cochlear implantation after this 6-month evaluation.

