### Randomisation procedure

Randomisation of CI versus observation was based on a 1:1 ratio and was stratified per centre. The allocation sequence was randomly generated by a computer (Stata SE 11.2, ralloc procedure), providing a sequence of treatments randomly permuted in blocks of varying size [2, 4, 6]. There was no blinding procedure in this open-label trial; however randomisation was centralised at the Toulouse University Hospital and managed by the project manager and clinical research associates. The allocation sequence was unknown to the investigators who enrolled participants.

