### Population and sample size

The sample size was calculated based on the expected number of failures of CROS hearing aids, BC trials and on the expected improvement of quality of life in cochlear implanted subjects with SSD/AHL. In a pilot study performed in our centre (unpublished), 40 to 50% of SSD/AHL subjects declined both CROS and BC devices after a three-week trial. This rate is consistent with previous studies performed on BC implantation after a headband trial (45% in Desmet et al. [33]). An improvement in quality of life is expected in these subjects after cochlear implantation, but it is not as significant as in patients with bilateral severe-to-profound deafness. A recent meta-analysis performed on traditional CI candidates with severe-to-profound deafness demonstrated an improvement of 1.05 standard deviations. To detect an improvement of 0.8 standard deviations with an alpha risk of 5% and an 80% power, 50 subjects (25 per arm) are necessary. Altogether, and to compensate the risk of dropouts, 150 subjects are included in this study.

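### The CI-versus-observation regression adjusts for one baseline value although three pre-randomisation evaluations exist; averaging them for the patient-reported outcomes is a cheap, modest gain in precision

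*Protocol article*

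**What the plan says.** For the randomised phase, the Protocol article (Statistical methods, data reporting and analysis) compares each 6-month outcome by t or Wilcoxon test and by "linear regressions adjusted for the baseline value". The value is in the singular and is not defined there. Secondary outcome measures says participants complete the questionnaires and hearing tests "at inclusion and 6 months after their choice of the treatment", which points to inclusion as the baseline.

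Study design and setting describes more data than that. A reference evaluation is made first, and then "The evaluation of quality of life, binaural hearing abilities, and tinnitus severity is repeated after the first trial (CROS) and the second trial (BC"). Choice of treatment and randomisation follow. Interventions confirms that every subject goes through both device trials, three weeks each.

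The sample size (Population and sample size) is set for one comparison: "To detect an improvement of 0.8 standard deviations" "with an alpha risk of 5% and an 80% power", "50 subjects (25 per arm) are necessary".

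**The concern.** A randomised subject has three evaluations of quality of life, hearing and tinnitus before allocation. All three are legitimate covariates, because none can be affected by the arm assigned. The stated model appears to use only the one furthest from randomisation, at least six weeks (two three-week trials) earlier.

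With about 25 subjects per arm, precision is scarce. A single questionnaire score carries occasion-to-occasion noise, and averaging several scores reduces it. If the repeats behave like further readings of the same state, the adjusted difference becomes more precise with no new visit. How far they do so is the whole question, since two of the three follow a period with a trial device.

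**Working it through.** **The plan's own figure.** Inputs: effect 0.8 SD, alpha 5% (two-sided reproduces the figure; one-sided gives 20 per arm), power 80%, and "Randomisation of CI versus observation was based on a 1:1 ratio". Then n per arm = 2(1.960 + 0.842)² / 0.8² = 24.5, rounded up to 25, or 50 in total. The exact t-test has 79.1% power at 25 per arm. The 50 reproduces and assumes no covariate, so the number of baselines does not affect it.

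**One baseline against the mean of three.** The article gives no correlations; every r below is an assumption. Let r be the correlation of the inclusion value with the 6-month value, with unit variances.

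- Residual variance with inclusion alone: 1 − r².
- With the mean of three exchangeable values (every pairwise correlation r): 1 − 3r²/(1 + 2r).

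| r | inclusion only | mean of three | reduction | power at 0.8 SD, 25 per arm |
|---|---|---|---|---|
| 0.3 | 0.910 | 0.831 | 9% | 81.9% → 85.2% |
| 0.5 | 0.750 | 0.625 | 17% | 88.6% → 93.4% |
| 0.7 | 0.510 | 0.388 | 24% | 97.0% → 99.3% |

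This is the best case.

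**Allowing for device trials.** Suppose each post-trial score carries extra independent noise with variance k(1 − r), that is, k times the ordinary occasion-to-occasion variance 1 − r. The noise variance of the mean of three is then (1 − r)m, with m = 1/3 + 2k/9, and the residual variance is 1 − r²/[r + (1 − r)m]. At r = 0.5 and k = 1, m = 0.556 and the residual variance is 1 − 0.25/0.778 = 0.679; 0.679/0.750 = 0.905, a 9.5% reduction.

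| r | k = 1 | k = 2 | k = 3 | k = 4 |
|---|---|---|---|---|
| 0.3 | 4.5% | 1.8% | 0 | −1.3% |
| 0.5 | 9.5% | 4.2% | 0 | −3.3% |
| 0.6 | 12.2% | 5.5% | 0 | −4.6% |
| 0.7 | 14.8% | 6.9% | 0 | −6.0% |

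Break-even is m = 1, so k = 3 whatever r is. The mean loses only if the device trials add more than three times the ordinary occasion-to-occasion variance.

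**Post-trial values that predict less well.** Let the post-trial values correlate a with the outcome, and let all three pre-randomisation values correlate b with one another. The mean explains (r + 2a)²/(3 + 6b).

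- r = 0.5, a = 0.5, b = 0.7: 2.25/7.2 = 0.3125; residual 0.688, an 8% reduction.
- r = 0.5, a = 0.40, b = 0.6: 1.69/6.6 = 0.256; residual 0.744, a 1% reduction.
- r = 0.5, a = 0.35, b = 0.7: 1.44/7.2 = 0.200; residual 0.800, 7% worse than inclusion alone.
- r = 0.7, a = 0.49, b = 0.7: 1.68²/7.2 = 0.392; residual 0.608, 19% worse.

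In the last two rows a = r × b: once the inclusion value is known, the later values add nothing. With ordinary measurement error, that requires a nearly error-free inclusion score.

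**Three separate covariates instead of the mean.** Two further covariates at N = 50 cost a factor of about 46/44 = 1.045. At r = 0.5, a = 0.40, b = 0.6 a 3% gross reduction becomes about a 1% loss; where the later values add nothing, the loss is about 4.5%.

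**The case against.** The strongest case against is that the later evaluations are not replicate baselines. Interventions speaks of auditory outcomes obtained with each device, and the secondary objectives use these evaluations to measure the effect of each successive intervention. That stands for SNR50 and localisation. For those tests neither averaging nor separate covariates can be recommended, and the inclusion value should stay.

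For the patient-reported outcomes the objection is weaker. Study design and setting randomises only subjects in whom neither trial was considered successful, so their scores may lie near the reference state. The Background calls a device effect on tinnitus most plausibly absent. Neither point proves exchangeability, so the gain must stay a range.

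Several stronger readings are tempting and are not supported:

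- **The analysis is wrong.** Single-baseline adjustment is valid and unbiased.
- **The trial is underpowered for want of the extra values.** The 50 rests on an unadjusted comparison, and at 0.8 SD with r = 0.5 one baseline already gives 88.6% power.
- **The regression weakens the ICUR.** The formula under Primary outcome measure uses raw mean costs and raw mean QALYs, with bootstrap uncertainty. The regression does not enter it.
- **The covariate is certainly the inclusion value.** That is an inference from Secondary outcome measures. Interventions also uses the word baseline for the assessment of each device trial, and a fuller plan may define it.

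**Conclusion.** The point holds as an optional, low-cost improvement in precision for the patient-reported outcomes. The facts are firm: one covariate value is named, and three evaluations precede allocation. The size is not.

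Under plausible assumptions (r from 0.3 to 0.7, device noise from one to three times the ordinary occasion-to-occasion variance), the mean of three lowers residual variance by roughly 0 to 14%; one corner of the grid reaches 14.8%. A 14% reduction is worth about 50/0.86 = 58 subjects instead of 50. The 17 to 24% figures need exchangeable values with a common correlation of 0.5 to 0.7. A loss is possible if the device trials strongly disturb the scores. It is small in the noise model, and larger only where the inclusion score is nearly error-free. The primary ICUR gains nothing unless its own calculation is changed.

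**What to change.** In Statistical methods, data reporting and analysis:

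- State which evaluation is the baseline value.
- For EQ-5D utility, EQ-VAS, NCIQ and tinnitus VAS, adjust for the mean of the available inclusion, post-CROS and post-BC values. Keep the inclusion-only model as a sensitivity analysis.
- For SNR50 and localisation, adjust for the inclusion value only.

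If the primary result is to benefit, make a separate change under Primary outcome measure: adjust the QALY difference in the ICUR for pre-randomisation EQ-5D utility, re-estimated in each bootstrap sample.

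**Cost.** No new data. The article does not list which questionnaires are completed at the post-trial evaluations, so check that each exists. A rule for a missing post-trial value is needed; the mean of the available values serves. Trial status reports inclusions complete and data controls ongoing in an open-label trial, so the change must be justified and documented before database lock.

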## Discussion

The detrimental consequences of SSD and AHL have been demonstrated for auditory performances as well as for the quality of life experienced by the patients [8, 51]. However, most studies emphasise the large variability of these consequences, with SSD subjects achieving near-normal localisation accuracy [52–54] or speech understanding in noise [52]. Likewise, the impact on quality of life varies considerably both on specific and generic questionnaires [8, 53] and the role of associated incapacitating symptoms such as tinnitus should be underlined [8].

The present protocol attempts to give account for this heterogeneity through the wide inclusion criteria which have been chosen. The choice of treatment and the outcomes of different subgroups (subjects with incapacitating tinnitus, SSD subjects, AHL subjects, and subjects with long lasting profound deafness) will therefore be specifically described. The theoretical advantage of cochlear implantation over CROS hearing aids and BC implants is to restore an auditory stimulation of the poor ear. This represents the mandatory condition to restore, at least partially, the perception of interaural differences. Further, alleviation of tinnitus is an established side-effect of CI, and subjects with incapacitating tinnitus associated with SSD/AHL might benefit more from this treatment than other SSD/AHL subpopulations.

The current study falls within the framework of validation of SSD/AHL as a new indication of cochlear implantation in France. In this line, the NCIQ was chosen as specific subjective evaluation of hearing before and after treatment, to refer to previous studies on benefits of CI in bilateral severe-to-profound deafness [32, 55–58]. Even though most reports on CI in SSD/AHL used the Speech, Spatial and Qualities of hearing to assess binaural benefits of CI in this population, the NCIQ allows a global evaluation of hearing handicap with several items referring to social limitations and psychological consequences of deafness. Further, this instrument was also used in several studies on CI in SSD/AHL [59].

The calculation of an intervention utility relies on a generic evaluation of quality of life. Among the different instruments which may be used, the Health Utility Index Mark 3 has been identified as sensitive to detect hearing changes after a treatment [51, 60]. Nevertheless, the EQ-5D is still the instrument which is recommended by the French Health Authority (HAS, Haute Autorité de Santé) as well as the preferred instrument recommended by NICE in the UK and the FDA in the USA in the framework of the Health Technology Assessment [61, 62]. It yields an exhaustive measure combining into a single score, both the symptoms of the disease, with its various physical, sensory, cognitive effects and the adverse effects of treatment.

The present study is the first randomised controlled trial on CI in SSD/AHL with the determination of the cost-utility ratio as a primary endpoint. It also provides an assessment of hearing modifications which may be expected from most of treatments for SSD/AHL, such as CROS systems and BAHA. Eventually, it will help delineating the national new criteria for CI indication.

### Trial status

Inclusions completed. Data controls ongoing.

## Abbreviations

AHL: Asymmetric Hearing Loss
BAHA: Bone-Anchored Hearing Aid
BC: Bone conduction
BIA: Budget Impact Analysis
CI: Cochlear Implant
CONSORT: Consolidated Standards Of Reporting Trials
CROS: Controlateral Routing of the Signal
CUAC: Cost-Utility Acceptability Curve
DRG: Disease Related Groups
FDA: Food and Drug Administration
FSHI: French Social Health Insurance
HUI-3: Health Utilities-3
ICUR: Incre mental Cost-utility Ratio
NCIQ: Nijmegen Cochlear Implant Questionnaire
NICE: National Institute for Health and Care Excellence
PTA: Pure Tone Average
SNR: Signal/Noise Ratio
SSD: Single Sided Deafness
SSQ: Speech, Spatial and Qualities Hearing scale
VAS: Visual Analogue Scale
